### Laboratory analyses

During the study, blood, urine and tracheal samples are collected. Separate parental informed consent is asked for taking, analysing and storing these samples.

Blood, urine and tracheal samples are taken within the first 2 hours of life and on days 3, 7, 14 and 28. Blood sampling is only done if a central or peripheral line is present and in combination with routine laboratory measurements. Urine sampling is only done if the patient has a urine catheter. Sampling of tracheal aspirates is only done during routine suctioning. In that way, sampling of laboratory markers are of minimal burden for the patient.

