**Methods/design:**

This trial is designed as a multicentre trial in which 400 infants (200 in each arm) will be included. Primary outcome measures are BPD, described as oxygen dependency by day 28 according to the definition of Jobe and Bancalari, and/or mortality by day 28. All liveborn infants with CDH born at a gestational age of over 34 weeks and no other severe congenital anomalies are eligible for inclusion. Parental informed consent is asked antenatally and the allocated ventilation mode starts within two hours after birth. Laboratory samples of blood, urine and tracheal aspirate are taken at the first day of life, day 3, day 7, day 14 and day 28 to evaluate laboratory markers for ventilator-induced lung injury and pulmonary hypertension.

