### Statistical analysis

We estimated that a total of 400 newborns can be included within a period of three years. In a previous study of the CDH study group, the incidence of BPD and/or death within the first 28 days of life is reported to be about 50% [9]. Assuming a difference of 15% in BPD and/or death within the first 28 days between both treatment groups, 186 patients are required per arm for a power of 80% at two-sided alpha is 0.05. To allow for some non-evaluable patients and dropouts, 200 patients per group will be included. To achieve equal distribution of the two ventilation modes among the participants, block randomization stratified per centre will be carried out. The data-analysis will be carried out at the Erasmus MC, Rotterdam. An intention-to-treat analysis will be performed. A p-value (two-sided) < 0.05 will be considered significant in all analyses.

The primary endpoint will be evaluated using multiple logistic regression analysis taking account of: centre, lung-to-head ratio, position of the liver (intra-abdominal or intra-thoracic) and the side of the defect (left, right or central). A subgroup analysis will be carried out in operated infants to evaluate the defect size, according to the CDH study group defect size scale (http://www.cdhsg.net).

The secondary endpoints will be evaluated by using the following statistical tests. Overall mortality in the first year of life will be analysed by Kaplan-Meier curves and Log rank tests. The chi-square test will be used to analyse number of treatment failures, presence of pulmonary hypertension according to echocardiographic parameters, requirement of medication at discharge and during the first year of life, and need for ECMO therapy (in ECMO centres). The Mann-Whitney test is used to evaluate the severity of chronic lung disease, number of days on the ventilator and the fraction of days with required medical treatment for pulmonary hypertension during the hospital admission. In the evaluation of the severity of chronic lung disease and the number of days on the ventilator, deaths are counted as worst outcome according to the intention-to-treat principle. Repeated measures ANOVA is used to evaluate levels of laboratory markers for ventilator-induced lung injury or pulmonary hypertension and pulmonary function at the age of six and twelve months. This analysis allows for missing data at different time points and is considered as the optimal way for evaluation of longitudinal data.

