All the above-mentioned analyses will allow for centre by stratification.

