### Study procedures

Parental informed consent will be obtained antenatally to enhance quick randomization. Following antenatal diagnosis, the parents are to be counselled and will receive information about the study, including a patient information letter and an informed consent form. If both parents decide to participate in the study, as soon as possible after birth central randomization will take place by the treating physician using a website. This way concealed allocation is guaranteed. Within two hours after delivery, the allocated ventilatory treatment has to be started.

The patient receives the allocated ventilation treatment during the entire admission period on the intensive care unit. During surgery, the child preferably remains on the allocated ventilation type, provided the treating surgeon agrees. Should the surgeon opt for the other ventilation mode, the patient is switched to the allocated ventilation treatment again after surgery. If the patient has to be re-intubated within the first 60 days after the start of the allocated treatment, the patient receives the allocated treatment again. Patients are observed up to day 60 after birth or until discharge whichever comes first. In Figure 1, an overview of the study procedures is given.

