#### Urine samples

Two urine samples from an 8-hour urine collection are taken to measure desmosine, an elastolytic degradation product of elastin. It gives an indication of the degradation of lung elastic fibres in ventilated neonates. One sample of 20 ml containing 0.2% boric acid and one sample of 10 ml will be stored at -20 degrees Celsius. Desmosine will be measured by mass-spectrometry, a highly sensitive way of measuring this laboratory marker [33,34].

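### The first marker sample (0-2 h) overlaps the start of the allocated mode and has no baseline role in the marker analysis; using it as a covariate would gain precision

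*Protocol article*

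**What the plan says.** The Laboratory analyses section fixes the sampling times: "Blood, urine and tracheal samples are taken within the first 2 hours of life and on days 3, 7, 14 and 28". The Study procedures section gives the intervention the same window: "Within two hours after delivery, the allocated ventilatory treatment has to be started". Neither section says which comes first.

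The Statistical analysis section says: "Repeated measures ANOVA is used to evaluate levels of laboratory markers for ventilator-induced lung injury or pulmonary hypertension". It supports this choice as follows: "This analysis allows for missing data at different time points and is considered as the optimal way for evaluation of longitudinal data". The only adjustment stated for these analyses is centre: "All the above-mentioned analyses will allow for centre by stratification". No baseline covariate or change from baseline is named, and the tested term (average arm effect or arm-by-time) is not given.

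Two other places bear on the first sample. The abstract words it more widely: "Laboratory samples of blood, urine and tracheal aspirate are taken at the first day of life, day 3, day 7, day 14 and day 28". The Urine samples section says: "Two urine samples from an 8-hour urine collection are taken to measure desmosine". Sampling is also conditional on routine care. For blood: "Blood sampling is only done if a central or peripheral line is present and in combination with routine laboratory measurements". Similar conditions apply to urine and tracheal aspirate.

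**The concern.** A sample drawn in the first two hours may precede the allocated mode or follow its start by up to two hours. For blood and tracheal aspirate it is plausibly close to a pre-treatment value. Such a value is most useful as a baseline that removes variation between infants. As one more response it would add a time point with little or no treatment effect to the comparison and leave the differences between infants in the error term.

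The markers are the laboratory evidence for a stated secondary aim, namely ventilator-induced lung injury and pulmonary hypertension. What is at stake is the chance of detecting a real marker difference from samples that are collected anyway. The order of sample and mode start cannot be recovered later unless both times are recorded.

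**Working it through.** **Plan's own figure.** The article gives no power or sample size for the markers. Its 186 per arm concerns the primary endpoint. The continuity-corrected two-proportion formula gives 183 (50% vs 35%) or 187 (57.5% vs 42.5%), so 186 is credible, but it does not bear on this point.

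**Inputs from the article.** There are five sampling times, the first at 0-2 h. The mode starts at 0-2 h. At most 200 infants per arm are sampled; separate consent is asked for sampling, so the true number is unknown.

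**Assumptions (not in the article).** Unit variance at each time, a constant effect d on days 3-28, no effect on the first sample unless stated, complete data, and correlation ρ = 0.3, 0.5 or 0.7.

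**Step 1: dilution of the average arm effect.** With five responses the mean effect is (0 + 4d)/5 = 0.80d. If the first sample already carried 25% of the effect, it is (0.25 + 4)d/5 = 0.85d. If late samples are missing and only 4, 3 or 2 samples exist, (k-1)/k leaves 75%, 67% or 50%.

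**Step 2: information under equal correlation (compound symmetry).** Information is effect² / variance, in units of d².
- All five averaged: 0.64 / [(1+4ρ)/5]
- Days 3-28 averaged, unadjusted: 1 / [(1+3ρ)/4]
- Days 3-28 adjusted for the first value: 1 / [(1+3ρ)/4 - ρ²]

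| ρ | All five | Adjusted | Ratio |
|---|---|---|---|
| 0.3 | 0.64/0.44 = 1.45 | 1/0.385 = 2.60 | 1.8 |
| 0.5 | 0.64/0.60 = 1.07 | 1/0.375 = 2.67 | 2.5 |
| 0.7 | 0.64/0.76 = 0.84 | 1/0.285 = 3.51 | 4.2 |

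At ρ = 0.5 the unadjusted days 3-28 mean has 1/0.625 = 1.60. The factor 2.5 is therefore 1.5 from taking the first sample out of the average, times 1.67 from adjusting for it.

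**Step 3: the same with correlation decaying by visit, ρ^|i-j|.** At ρ = 0.5:
- The five-sample mean has variance 0.445, so information is 0.64/0.445 = 1.44.
- The days 3-28 mean has variance 0.516. Its covariance with the first value is (0.5 + 0.25 + 0.125 + 0.0625)/4 = 0.234.
- The adjusted variance is 0.516 - 0.234² = 0.461, so information is 2.17.
- The ratio is 2.17/1.44 = 1.5.

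At ρ = 0.3 and 0.7 the ratio is 1.3 and 2.0. Adjustment alone, against unadjusted days 3-28, contributes 1.03, 1.12 and 1.41 at the three values of ρ.

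**Step 4: power if arm-by-time is tested instead.** This uses 200 per arm, d = 0.25, two-sided 0.05 and equal correlation. The interaction has 4 df and noncentrality (n/2)(0.8d²)/(1-ρ), which is 7.1, 10.0 and 16.7.

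| ρ | Average of all five | Arm-by-time | Adjusted for first value |
|---|---|---|---|
| 0.3 | 85% | 55% | 98% |
| 0.5 | 73% | 72% | 98% |
| 0.7 | 63% | 92% | 99.7% |

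With 100 per arm and the same d, arm-by-time has 29%, 39% and 62%, against 81%, 82% and 91% with adjustment. The same order held in the other cases computed (d up to 0.40).

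**Step 5: urine.** An 8-hour collection that starts no earlier than birth has at least 8 - 2 = 6 hours after the two-hour deadline for starting the allocated mode. It cannot be complete within the first 2 hours of life.

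**The case against.** The strongest objection is that the article does not say the first value is a response, or that the average arm effect is the test. A reader might infer that the plan dilutes the marker effect by one fifth. The text does not support that: it names a method and an outcome, not the tested term, and in an arm-by-time test the first sample acts as a reference and nothing is diluted. The role of the first value could also be settled in an analysis plan that is not shown. This stands, and the dilution is therefore conditional. It does not remove the point, because the article itself names the analysis and its centre adjustment and calls the method optimal, while a more precise use of the same samples is available.

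The larger ratios need a 0-2 h value to correlate with day 28 as strongly as day 14 does. This stands too. With decaying correlation the gain is smaller, and at ρ = 0.3 nearly all of it comes from leaving the first sample out of the average.

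A reader might also infer that a chance imbalance at birth biases the result. It does not: under randomisation the unadjusted comparison keeps its type I error. Only precision is affected.

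Nor can the first value be taken as untreated for every sample type. Urine is the clear exception. For blood and tracheal aspirate the claim depends on when the sample was drawn. If the first value already carries a treatment effect, adjusting for it would remove part of the effect sought.

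Finally, sampling depends on a line, a catheter or routine suctioning, so first values will sometimes be missing, and time stamps cannot be introduced prospectively for infants already included.

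**Conclusion.** The point holds as one about efficiency and definition. The first sample and the start of the allocated mode share an unordered 0-2 h window, and the stated analysis gives that sample no baseline role. Using it as a covariate, with days 3-28 as responses, gives about 1.8-4.2 times the information of averaging all five samples under compound symmetry, and about 1.3-2.0 times if correlation decays by visit. If the average over five samples is tested, about 80% of the effect remains. If arm-by-time is tested there is no dilution, but power was lower than with adjustment in every case computed; those cases all assume compound symmetry.

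Effect size, correlation, numbers sampled and the absence of an effect on the first sample are assumptions. Only secondary outcomes are affected. For urine desmosine the sampling descriptions conflict, and a baseline role is not supported as they stand.

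**What to change.** - Record the clock time of the first sample and of the start of the allocated mode.
- For blood and tracheal markers, model days 3, 7, 14 and 28 with arm, time, arm-by-time and centre, adjusting for the first value. Alternatively, use a longitudinal model that constrains baseline means to be equal in both arms, which keeps infants without a first sample.
- Add a sensitivity analysis restricted to first samples drawn before the allocated mode started.
- For urine desmosine, reconcile the abstract (first day of life), the Laboratory analyses section (first 2 hours) and the Urine samples section (8-hour collection). Do not treat the first value as a pre-treatment baseline unless the collection times support it.

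The cost is two time stamps, a few sentences of analysis wording and a rule for missing first samples. No extra sample is needed.

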#### Blood samples

Blood markers are determined by immuno-assay analysis and are necessary support evidence of chronic lung disease and to further evaluate its severity [28-32].

The following laboratory markers are measured:

• Markers for inflammation and pulmonary vascular endothelial dysfunction and pulmonary hypertension (intercellular adhesion molecule (ICAM), vascular cell adhesion molecule (VCAM), sP- and sE-selectine, pro-brain natriuretic peptide (Pro-BNP), vascular endothelial growth factor (VEGF), von Willebrand factor, thrombomodulin, factor VIII and Asymmetric Dimethylarginine (ADMA)

• Markers for the nitroxide pathway (nitrate and nitrite)

#### Urine samples

Two urine samples from an 8-hour urine collection are taken to measure desmosine, an elastolytic degradation product of elastin. It gives an indication of the degradation of lung elastic fibres in ventilated neonates. One sample of 20 ml containing 0.2% boric acid and one sample of 10 ml will be stored at -20 degrees Celsius. Desmosine will be measured by mass-spectrometry, a highly sensitive way of measuring this laboratory marker [33,34].

#### Tracheal aspirate

Protein profiling by proteomics are used for identifying specific groups of proteins, which are involved in the pathogenesis of chronic lung disease. During routine tracheal suctioning, flushing with 0.5-1.0 ml saline is performed according to standard practice. The tracheal aspirates are centrifuged for 10 minutes at 3000 rpm and are stored at -80 degrees Celsius [35,36].

### Follow-up

At all participating centres, routine follow-up takes place at the age of 6 months, 12 months, 24 months, 5 years, 8 years, 12 years and 18 years in all patients with CDH, including participants of the VICI-trial. During follow-up visits, routine physical examination and additional testing (e.g. lung function tests or developmental tests) take place. For the purpose of this study, parents complete a patient diary card on a daily basis for one month at the age of six and twelve months. By using this diary card information about whether their child coughed, wheezed and/or needed medication is collected. This gives a quantitative assessment of morbidity.

In a subgroup of patients born at the Erasmus Medical Centre and King's College Hospital, lung function tests are performed at the age of six and twelve months. Only these two centres have the equipment and expertise to measure lung function in children below the age of one. At King's College, FRC (functional residual capacity) and LCI (lung clearance index) are measured by using helium gas dilution. The LCI is the cumulative expired volume required to clear an inert gas from the lungs, divided by the FRC. Also, lung function tests are performed before and after bronchodilation at this centre. Therefore, a bronchodilator is administered by a face mask and a spacer. At the Erasmus Medical Centre, the FRC is determined by plethysmographic measurements and the LCI is defined by SF6 measurements.

Since the methods of lung function measurements differ between the two centres, these measurements will be analysed separately for both centres.

### Safety reporting

An adverse event or complication is defined as any undesirable occurrence in a patient. Mortality is regarded a serious adverse event. Adverse events or complications are reported to the study coordinator within 24 hours. Thereafter, the study coordinator informs the data safety monitoring board, who monitors the incidence of mortality on a continuous base. If at some point a large difference in mortality between the two treatment groups is noticed, the data safety monitoring board may recommend ending the study.

### Data collection

Demographic and neonatal characteristics as well as data on the clinical course and treatment of all patients will be collected in a central database in Rotterdam. Corporeal material collected during the study is stored at the local centres.

Since it should be impossible to identify a specific patient, data are sealed by a code and a patient number replaces personal data. All centres keep a logbook of the number of eligible non-participants, including the reasons for not participating.

Patient data are stored during the study and for fifteen years after the study has ended. If the parents consent, corporeal material is also stored for fifteen years after the study has ended. This material may be used in future for a study with the same research aims.

### Ethical approval

The first of October 2008, this study has been given approval by the medical ethics committee of the ErasmusMC Rotterdam. Thereafter, the local medical ethics committees of eleven participating centres gave their approval. In one centre, ethical approval is still being sought. Once a year, a summary of the trial's progress is send to the medical ethics committee of the ErasmusMC, Rotterdam, the Netherlands. Information is provided on the numbers of subjects included, (serious) adverse events, other problems and amendments. New participating centres are still included. We will continue recruiting patients for our trial until we reached the number of 400 participants. Our goal is to have this amount of patients included by the first of October 2013.

## Discussion

Congenital diaphragmatic hernia (CDH) is associated with a high risk pulmonary morbidity [6]. Several previous studies have reported a wide range of pulmonary problems throughout childhood in these patients [6]. A recent study of our group in collaboration with the CDH Registry reported a 41% prevalence of bronchopulmonary dysplasia (BPD) in survivors of CDH [9]. This study reported the initial ventilation mode to be possibly associated with BPD in these patients. This formed the rationale for our study, which aims at comparing HFO and conventional ventilation as initial ventilation modes in infants with CDH.

Our study is the first randomized clinical trial in the field of CDH. Previous studies were retrospective or observational reports, mostly from single centres. Moreover, progress in CDH research is hampered due to small numbers of patients and lack of evidence-based treatment strategies. Cooperation between centres is therefore highly important to enhance research, exchange knowledge and compare data in larger groups of patients. The CDH Study Group is an example of a worldwide network which has established a large database on CDH patients. To date, the CDH Study Group has published numerous reports in the field of CDH, which contain valuable information on survival, treatment strategies and morbidity in infants with CDH. Another example is the CDH-EURO consortium, a European collaboration between tertiary centres with an expertise in treatment of CDH, which also initiated the VICI-trial. The consortium also developed a recently published standardized treatment protocol [4]. This treatment protocol makes valuable comparison of patient data possible, since all CDH patients, including the VICI-trial patients, born in these centres are treated according to this protocol.

HFO and conventional ventilation are both safe, effective and widely used strategies to ventilate infants with respiratory distress. Although observational and retrospective studies have suggested that HFO may improve survival and pulmonary outcome in infants with CDH, no prospective randomized controlled trials have been carried out to compare initial ventilation strategies in these patients. Therefore, no specific conclusions about certain benefits or disadvantages of either HFO or CMV can be made.

As the first randomized clinical trial in CDH infants, the VICI-trial will provide a clearer view on ventilatory treatment strategies and possible prevention of mortality and morbidity. Still, there are many questions left in the field of CDH and clinical trials are highly needed to improve care and establish standardized treatment. Cooperative networks between centres, such as the CDH-EURO consortium, play a major role in this.
